**Figure 1 F1:**
[figure not shown]
**The trial and the control municipalities in Pirkanmaa area in south-western Finland**.

For the cluster randomisation, the municipalities were arranged into matched pairs and within each pair they were randomized to an trial and a control municipality. The pair-matching was done with regard to number of births, size and socio-economic level of the population, estimated incidence of GDM and whether the clinic situated in rural or urban area. Municipalities were randomized rather than individual clinics, nurses or pregnant women to avoid contamination.

In Finland, maternity health care is provided by the municipalities and funded through public taxation. The visits are free of charge for women. Almost all pregnant women (99.7%) utilize municipal maternity care services, although there are private services available as well [5,31]. Currently, first-time pregnant women are recommended to visit a nurse 11-15 times and a physician three times during pregnancy [31,32]. The recommended number of visits is lower (7-11) during subsequent pregnancies. The first visit to maternity clinics usually takes place when women are at approximately 8 to 12 weeks' gestation. The spouses are encouraged to attend all visits.

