### Recruitment of study population

In total, 23 nurses from the trial clinics and 30 nurses from the control clinics participated in the implementation of the study. The nurses recruited pregnant women when they contacted the maternity clinic for the first time by telephone (up to 12 weeks' gestation). The women who were interested in participating in trial received an invitation letter and the informed consent form by mail. The eligible women willing to participate signed the informed consent during the first maternity visit. If the women were not eligible or not willing to participate, they were asked to complete a baseline questionnaire and another informed consent for later linkage to the birth registry information.

The nurses used structured form to keep record on the women invited and eligible to the study and of those eligible or not wanting to participate. The form also included space for entering the reasons for dropping out. Recruitment was planned to continue until at least 30 women were enrolled in each municipality. All participants of the trial including the non-participants who were willing to fill the baseline questionnaire, were included in the follow-up study. Ethical approval for this study was obtained from the Ethical board of Pirkanmaa Hospital District (Reference number R06230, 19.1.2007).

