### Power calculations and sample size

The randomization of maternity clinics as clusters instead of women as individuals was taken into account in the power calculations [66]. When planning the RCT, no published studies on prevention of GDM among women at risk or data on decrease in the incidence of GDM were available. The power calculations for pair-matched study were based on the assumption of detecting a 40% reduction of incidence of GDM from 40% in the control clinics to 24% in the trial clinics. The power of the study was 0.80, significance level 0.05 and coefficient of variation of rate between clusters, indicating cluster sampling, 0.1. The dropout rate during the study (estimated 25%) was taken into account in the sample size calculations. Thus, a total number of 560 women should be recruited to the study. The number of women in the end of the study would thus be 210 + 210 (7+7 clinics, 30 women/clinic).

Success in recruitment and proportion of drop-outs (25%) were estimated based on the pilot study [28,67]. Our recruitment target seemed feasible since the annual number of deliveries in Pirkanmaa region was approximately 5000 [31] and at least fourth of these women were estimated to fulfill the inclusion criteria of this study.

The sample available for the 1-year follow-up (n = 462) is adequate to discover 5-20% difference of metabolic syndrome in trial and control groups. Intracluster correlation coefficient in the current study is estimated as 0.12 (valid when 0.10-0.30) [68].

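### With the stated ICC of 0.12, 462 women at 1 year do not give adequate power across a 5-20% difference in metabolic syndrome

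*Protocol article*

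**What the plan says.** All the relevant statements are in the protocol article.

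- Power calculations and sample size, on the 1-year follow-up: "The sample available for the 1-year follow-up (n = 462) is adequate to discover 5-20% difference of metabolic syndrome in trial and control groups".
- The sentence after it: "Intracluster correlation coefficient in the current study is estimated as 0.12 (valid when 0.10-0.30".
- The same section, on the number of clusters: "The number of women in the end of the study would thus be 210 + 210 (7+7 clinics, 30 women/clinic".
- Study design, setting and group allocation, on the randomised unit: "Municipalities were randomized rather than individual clinics, nurses or pregnant women to avoid contamination". The allocation was paired: "the municipalities were arranged into matched pairs and within each pair they were randomized to an trial and a control municipality".
- Power and alpha are stated once, for gestational diabetes: "The power of the study was 0.80, significance level 0.05 and coefficient of variation of rate between clusters, indicating cluster sampling, 0.1".

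For metabolic syndrome the article gives no control rate, power, alpha or design effect. It does not say whether the 5-20% means 5% in one arm against 20% in the other, or an absolute difference of 5 to 20 percentage points.

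**The concern.** An adequacy statement and a large ICC stand side by side, and the design has few clusters. With 14 clusters, an ICC of 0.12 removes most of the information in 462 women, so a claim reaching down to a 5% difference needs checking.

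Metabolic syndrome is one of several outcomes listed for the 1-year follow-up. If the article says the sample is adequate for differences as small as 5%, a non-significant result could be taken as evidence that the counselling has no worthwhile effect at 1 year, when the design could not have shown such an effect.

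**Working it through.** **The primary calculation, for comparison.** The article plans on "detecting a 40% reduction of incidence of GDM from 40% in the control clinics to 24% in the trial clinics", with a between-cluster coefficient of variation k = 0.1 and 30 women per cluster. The pair-matched formula is

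pairs = 2 + (1.96 + 0.84)² × [(0.40×0.60 + 0.24×0.76)/30 + 0.1² × (0.40² + 0.24²)] / 0.16² = 6.98.

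That gives 7 pairs, 420 women completing, and 420/0.75 = 560 to recruit. The primary sample size therefore reproduces. The 1-year statement comes with too few inputs to reproduce, so it is tested against its own ICC.

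**Inputs.** From the article: n = 462, 14 municipalities, ICC 0.12 (0.10-0.30). Assumed: equal arms (231 each), equal clusters, two-sided alpha 0.05, 80% power as the meaning of adequate, and the ICC applying to the randomised municipality.

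**Effective sample size.**
- Women per cluster: 462/14 = 33.
- Design effect: 1 + (33 − 1) × 0.12 = 4.84.
- Effective n per arm: 231/4.84 = 47.7.
- At ICC 0.10: design effect 4.20, 55.0 per arm. At ICC 0.30: 10.6, 21.8 per arm.

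**Power.** Power = Φ(|p1 − p2| / √[(p1q1 + p2q2)/n] − 1.96). For 5% versus 20% at ICC 0.12: √[(0.0475 + 0.16)/47.7] = 0.0659; 0.15/0.0659 = 2.275; Φ(0.315) = 0.62. Using the pooled variance under the null gives 0.60. The table shows pooled to unpooled values.

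| Comparison | ICC 0 | ICC 0.10 | ICC 0.12 | ICC 0.30 |
|---|---|---|---|---|
| 5% vs 20% | >0.99 | 0.67-0.69 | 0.60-0.62 | 0.32-0.34 |
| 5% vs 10% | 0.53-0.54 | 0.17 | 0.15 | 0.09 |
| 10% vs 15% | 0.37 | 0.12 | 0.11 | 0.07 |
| 20% vs 25% | 0.25 | 0.09 | 0.08 | 0.06 |
| 5% vs 25% | >0.99 | 0.85-0.86 | 0.79-0.81 | 0.45-0.49 |
| 10% vs 30% | >0.99 | 0.75-0.77 | 0.69-0.71 | 0.38-0.40 |
| 20% vs 40% | >0.99 | 0.63-0.65 | 0.57-0.59 | 0.30-0.31 |

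**Can follow-up of more women help?** With 7 clusters per arm, effective n per arm cannot exceed 7/0.12 = 58. Power for 5% versus 20% then stays at or below about 0.69-0.71. Reaching 80% for that contrast with 462 women needs an ICC of about 0.065-0.068 or less, below the article's own range.

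**Reduction detectable at 80% power (unpooled formula, solved for the fall).** The intervention aims to lower risk, so the relevant difference is a fall from the control rate.

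| Control rate | ICC 0.10 | ICC 0.12 | ICC 0.30 |
|---|---|---|---|
| 15% | 14.0 points | 14.7 points | not reached |
| 20% | 16.6 | 17.4 | not reached |
| 25% | 18.7 | 19.8 | not reached |
| 30% | 20.5 | 21.7 | 28.5 |

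Not reached means that even a fall to zero has less than 80% power. At ICC 0.12 the same is true from a control rate of 10%, where complete elimination has power of about 0.61-0.63. The 14.7-point fall from 15% would leave 0.3%, which is close to elimination.

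**The case against.** The strongest reply is that several inputs are not the article's. It states no power, alpha, sidedness or control rate for this outcome, and it attaches the ICC to the current study without saying at which level. The analysis section models nurses as well as clinics. If 0.12 applied to the 53 nurses (about 8.7 women each), the design effect would be 1 + 7.7 × 0.12 = 1.93 and 5% versus 20% would have power of about 0.94-0.95. Pair-matching could also reduce the between-cluster variance.

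This justifies stating the assumptions, but it does not rescue the claim. Municipalities were randomised, so that is the level at which the ICC limits the comparison. No matching correlation is given, and a t reference distribution lowers the power for 5% versus 20% to 0.55 (12 df, unmatched) or 0.48 (6 df, seven pairs). One-sided alpha 0.05 raises it only to about 0.72-0.74. Even on the nurse-level reading, 5% versus 10% has power of only 0.31.

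A reader might also infer more than the documents support:

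- **That every part of the range is out of reach.** It is not: 5% versus 25% has about 0.79-0.81, and falls of 15 to 20 points are detectable from control rates of 15-25%.
- **That a 5-point difference could never be detected, even without clustering.** That depends on the base rate: 6% versus 1% has power of 0.84 at ICC 0.
- **That the design detects only differences of about 23-27 points.** Those figures describe rises above a base of 10-30%, whereas the trial looks for falls.
- **That the 462 include women outside the trial.** The recruitment section does say that all trial participants, "including the non-participants who were willing to fill the baseline questionnaire, were included in the follow-up study", but the power sentence speaks of the trial and control groups, and nothing ties non-participants to the 462.

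**Conclusion.** The adequacy statement is not supported by the ICC printed next to it. Read as 5% versus 20%, power at ICC 0.12 is about 0.60-0.62, and it is below 0.80 over the whole stated ICC range (0.67-0.69 at 0.10, 0.32-0.34 at 0.30). Read as percentage points, the bottom of the range has power of about 0.08-0.15 from bases of 5-20%. Only the top of the range is attainable, and only when the lower of the two rates is about 5% or less.

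This rests on two-sided alpha 0.05, an 80% target, equal arms and cluster sizes, and the ICC acting at municipality level. Unequal clusters would lower power further. An effective matching could raise it by an amount the article does not allow one to calculate.

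The point concerns one of several 1-year outcomes. It does not touch the primary sample size, which reproduces. It should be corrected because a stated design property is wrong and the correction is cheap.

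**What to change.** - Say what the 5-20% means, and give the assumed control rate of metabolic syndrome, the power, alpha and sidedness, and the level at which the ICC applies.
- Replace the adequacy claim with the reduction detectable at 80% power. At ICC 0.12 this is about 15 points from a control rate of 15%, 17 from 20%, 20 from 25% and 22 from 30%.
- Give the range over ICC 0.10-0.30. At 0.30 no fall from a control rate of 25% or lower reaches 80% power, and about 28 points is needed from 30%.
- Present the 1-year metabolic syndrome comparison as an estimate with a confidence interval that allows for clustering, not as an adequately powered test. For scale, with 20% in both arms and ICC 0.12 the 95% interval would be about ±1.96 × √(2 × 0.20 × 0.80/47.7) = ±16 points.

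The cost is a less favourable stated figure. No additional women, visits or measurements are needed.

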### Statistical analysis

The main method in the comparison of the trial and the control group is the multilevel analysis. In the multilevel analysis, both individual-level, nurse-level and clinic-level influences on the outcomes can be examined simultaneously and the results are corrected for between-clinic and between-nurse variation. Also non-parametric methods will be utilized when applicable. The choice of method depends on the measurement scale and distribution of the outcome variable. Intention-to-treat principle is followed, i.e. the analysis is performed in originally randomized groups. Information on drop-outs is received through linkage to birth registry. Intention-to-treat analyses are performed after birth registry linkage. A secondary analysis is performed without the drop-outs.

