## Methods/Design

### Study design, setting and group allocation

The RCT was conducted in primary health care maternity clinics in Pirkanmaa region, situated south-western part of Finland (Figure 1). The prevalence of GDM was 17% in Pirkanmaa region in 2004[5]. Municipalities in Pirkanmaa region with at least 70 annual deliveries were contacted and recruited to the study (N = 14). The city of Tampere, with more than 200.000 inhabitants and 23 maternity clinics, was the biggest of these municipalities. However, it was the only municipality restricting the number of participating maternity clinics to one due to the extra workload accumulated to the nurses from the study arrangements and counseling. All clinics from the other municipalities took part in the study.

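### The model named for the analysis leaves out the randomised municipality and the matched pair, so read literally it does not secure the stated 0.05 and 0.80

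*Protocol article*

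**What the plan says.** On the design, the section on study design, setting and group allocation is explicit: "the municipalities were arranged into matched pairs and within each pair they were randomized to an trial and a control municipality", and "Municipalities were randomized rather than individual clinics, nurses or pregnant women to avoid contamination". There were 14 municipalities, hence 7 pairs. The same section treats a clinic as part of a municipality. Of the largest city it says that "it was the only municipality restricting the number of participating maternity clinics to one", and then: "All clinics from the other municipalities took part in the study". How many clinics the other 13 municipalities had is not given.

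The section on power and sample size describes a pair-matched calculation but names a different unit: "The randomization of maternity clinics as clusters instead of women as individuals was taken into account in the power calculations". It counts seven plus seven clinics with 30 women in each. The recruitment section sets the same 30 women per municipality.

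The Statistical analysis section makes multilevel analysis the main method, with individual, nurse and clinic levels, and states that "the results are corrected for between-clinic and between-nurse variation". It adds: "Also non-parametric methods will be utilized when applicable". It mentions neither municipality nor pair.

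**The concern.** The unit that was randomised should carry the error term for the treatment contrast. If a municipality holds several clinics and the model stops at clinic, clinics of one municipality count as separately randomised. Variation between municipalities then enters the contrast in full but is averaged over too many units in the standard error. The matched pair was used both to allocate and to size the trial, so leaving it out means that the analysis is not the one whose power was calculated. At stake are the 0.05 and 0.80 for the primary comparison of GDM, and the width of its confidence interval.

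**Working it through.** **1. Which analysis the sample size belongs to.** Inputs from the power section: control rate p0 = 0.40, trial rate p1 = 0.24, power 0.80, significance level 0.05 (taken as two-sided), coefficient of variation k = 0.1, n = 30 women per cluster, dropout 25%. The pair-matched cluster formula is

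c = 2 + (1.96 + 0.842)² × [p0(1−p0)/n + p1(1−p1)/n + k²(p0² + p1²)] / (p0 − p1)²

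- Bracket: 0.00800 + 0.00608 + 0.002176 = 0.016256
- Divided by 0.16² = 0.0256: 0.635
- Times 7.849: 4.98
- c = 2 + 4.98 = 6.98, so 7 pairs
- 7 × 30 = 210 per arm, 420 in all; 420/0.75 = 560, as stated. Power at 7 pairs is 80.1%.

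The unmatched version adds 1 instead of 2 and gives 5.98, so 6 clusters per arm and 6 × 30 × 2/0.75 = 480. The stated 560 therefore belongs to a paired comparison of 7 + 7 units.

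**2. The ICC implied by k.** (0.1 × 0.40)²/(0.40 × 0.60) = 0.0016/0.24 = 0.0067.

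**3. Standard error if the top level is clinic.** Assume 3 equal clinics of 10 women per municipality, all between-cluster variance ρ at municipality level, and no pair effect. The variance of a single binary outcome is 0.24.

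- True SE² = (2/7) × 0.24 × [ρ + (1−ρ)/30]. At ρ = 0.12: (2/7) × 0.24 × 0.1493 = 0.01024, SE 0.101.
- Expected clinic-level SE² = (2/21) × 0.24 × [ρ + (1−ρ)/10 − 0.1ρ]. The last term arises because 2 of the 20 other clinics in the arm share the municipality. At ρ = 0.12: (2/21) × 0.24 × 0.196 = 0.00448, SE 0.067.
- At ρ = 0.0067 the same formulas give 0.052 against 0.049.

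**4. Type I error by simulation.** 20,000 runs per setting, rate 0.40 in both arms, 7 pairs, 30 women per municipality. The test is a t test on clinic means, a simple stand-in for a multilevel model whose top level is the clinic.

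| Municipality ICC | Pair ICC | 1 clinic | 2 clinics | 3 clinics |
|---|---|---|---|---|
| 0.0067 | 0 | 5.1% | 6.1% | 6.5% |
| 0.02 | 0 | 5.2% | 7.8% | 9.2% |
| 0.05 | 0 | 5.0% | 10.8% | 13.6% |
| 0.12 | 0 | 5.1% | 13.9% | 19.4% |
| 0.0067 | 0.02 | 2.1% | 3.8% | 4.8% |
| 0.0067 | 0.05 | 0.9% | 2.3% | 3.1% |
| 0.02 | 0.02 | 2.5% | 5.4% | 7.1% |
| 0.05 | 0.05 | 1.8% | 6.0% | 9.3% |

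If the between-cluster variance lies wholly at clinic level (ICC 0.05), the clinic-level test holds 4.9-5.2%. A paired t test on municipality means (6 degrees of freedom) gives 4.7-5.3% in every setting.

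The cost of omitting the pair shows in the standard error. With one clinic per municipality, municipality ICC 0.0067 and pair ICC 0.05, the true SE is 0.051 and the unpaired estimate is 0.078.

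The numbers of clinics, the pair ICCs, the municipality ICCs of 0.02 and 0.05, and the split of variance between levels are assumptions. The plan supplies k = 0.1 and, in the paragraph on the 1-year follow-up, an ICC of 0.12.

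**The case against.** The strongest reply is that clinic in the analysis section means the randomised unit. The power section uses the word so, and the Discussion speaks of randomising clinic areas. On that reading the municipality level is present and nothing is inflated for want of it. This reading is possible but not secured, because the setting section uses clinic for a part of a municipality and contrasts the two. Even if it is right, the pair is still missing.

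The second reply concerns size. Three clinics in every municipality would make 42 clinics for 53 nurses, about 1.3 nurses per clinic, and the largest city supplied only one clinic. At the plan's own k = 0.1 the inflation reaches only 6.1-6.5%. The 0.12 is given for the follow-up outcome, not in the GDM calculation. All of this stands and limits the claim.

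A reader might infer that standard errors are certainly too small and the error rate certainly above 5%. The documents do not support that. Inflation needs several clinics per municipality, variance at municipality level, and clinic in its literal sense. Omitting the pairs pushes the other way, and matching on estimated GDM incidence among other factors makes a pair effect plausible.

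A reader might also infer a normal-theory Wald test, or rank tests on individual women that ignore clustering. The section states neither a reference distribution nor the unit for non-parametric tests, and such detail may stand in a fuller document. The point here rests only on the levels that the article does name.

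**Conclusion.** The point holds as a mismatch. Allocation and sample size are by paired municipality, the named model has neither municipality nor pair, and clinic carries two meanings. Taken literally, the model does not secure the stated significance level or power.

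The direction of the error cannot be settled from the documents. With 2 to 3 clinics per municipality and no pair effect, the type I error runs from about 6% (k = 0.1) through 8-9% (ICC 0.02) to 14-19% (ICC 0.12). With one clinic per municipality it is 5% without a pair effect and 0.9-2.5% with one. With several clinics and a pair effect it lay between 2.3% and 9.3% in the settings tabulated. These figures come from a cluster-level stand-in for the multilevel model and depend on the assumptions listed with them. That the paired municipality analysis keeps about 5% throughout does not depend on which of these settings is true.

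**What to change.** In the Statistical analysis section, state that the primary model has municipality as its top level, with clinic and nurse nested within it, and includes the matched pair. Alternatively, state that the primary comparison is a paired analysis of municipality-level summaries. Base degrees of freedom on 14 municipalities and 7 pairs (6 for the paired t test). State that any non-parametric test is done on municipality summaries or by permutation within pairs. In the power and Statistical analysis sections, use municipality for the randomised unit and keep clinic for the sub-unit.

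The cost is wording only; no further data or participants are needed. Confidence intervals may be somewhat wider than under the literal model, which the pair-matched sample size already allows for.

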## Discussion

The trial is expected to be effective in short-term prevention of gestational diabetes. The possible long-term benefits include prevention of chronic diseases, such as type 2 diabetes and cardiovascular diseases, both in mother and offspring.

The design of the study was a cluster-randomized trial instead of individual randomization. Contamination of nurses counseling practices would have been larger if individuals had been randomized instead of maternity clinic areas. Even though cluster randomization requires larger sample size, the results may be more easily applied to health care. Our purpose was not to build a design with maximal support for lifestyle modification, because it would not have been applicable in real health care setting. Embedding the trial into ongoing maternal care we aimed to increase the effectiveness rather than efficacy of the intervention.

Finland is one of the countries with nationally covering maternity center network funded by public taxation. If our trial was proved to be a cost-effective way to prevent gestational and perinatal complications it might be applicable and might have large public health impact even in those countries with different maternity care systems.

## Abbreviations

GDM: gestational diabetes mellitus; BMI: body mass index; OGTT: oral glucose tolerance test; RCT: randomized controlled trial; AUC: area under curve; RPE: visual scale of perceived exertion; LTPA: leisure time physical activity; MET: multiples of resting metabolic equivalents; FFQ: food frequency questionnaire; QALY: quality adjusted life years
